## Study objectives

The “usefulness of Myocardial work IndeX in ExtraCorporeal Membrane Oxygenation patients” (MIX-ECMO) study aims to study the association of non-invasive myocardial work indices with outcome in patients undergoing VA-ECMO therapy.

The primary objective measure is the failure to wean, which consists of different clinical outcomes suggesting the inability to free the patient from MCS:
•Failure to wean: Composite of cardiovascular mortality, need for long-term mechanical circulatory support (MCS) or heart transplantation at 30 days

Besides that, secondary objectives will be also investigated to examine all-cause mortality and certain endpoints of organ-failure:

Secondary outcome measures:
•All-cause mortality at 30 days•VA-ECMO-free days at 30 days•Need for renal replacement therapy during intensive care at 30 days•Successful weaning from mechanical ventilation at 30 days•Ventilator-free days at 30 days•Discharge from intensive care unit (ICU) at 30 days•Discharge from hospital at 30 days

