## Sample size and patient population

Patients undergoing VA-ECMO (regardless of the indication for the therapy) will be enrolled. The initial plan is to enroll patients within 1 year, with no loss to follow-up. Based on a previous VA-ECMO study investigating echocardiographic predictors of outcome (18), we estimated a 92.2% statistical power to detect a 20% effect with respect to the primary composite outcome, by assuming an 30% weaning failure rate in a sample size of 100 patients. Importantly, the feasibility of speckle-tracking analysis with transoesophageal echocardiography (TOE) was previously reported to be 90% (19). Therefore, we aim to enroll 110 subjects, a sample size which exceeds previous cardiac imaging studies of the field able to demonstrate association of echocardiography measures with outcome (18, 20). Both peripherally and centrally cannulated subjects are candidates for participation. Considering that the two populations are typically quite different in terms of indication for the therapy (ACS- or decompensated chronic heart failure-associated CS vs. cardiac surgery population), a balanced enrollment of the two methods will be facilitated by interim assessment at 50% of the enrollment. All LV venting options are eligible for enrollment, however, if utilized, the mode of LV unloading (central left atrial vent, Impella, transaortic LV pigtail catheter etc.) will also be collected. Notably, LV unloading significantly influences ventricular mechanics (21). Still, due to the highly variable institutional practices in terms of LV unloading, the study protocol does not exclude certain techniques.

The study aims to include a broad spectrum of patients; therefore, the exclusion criteria are mainly technical contraindications of the measurements. Patients 18 years or older on VA-ECMO will be enrolled, if TOE is feasible or the transthoracic echo window also enable sufficient image quality for further analysis. The inclusion and exclusion criteria are listed in Table 1.

**Table 1 T1:** Inclusion and exclusion criteria of the study.

Inclusion criteria	Exclusion criteria
Patients 18 years old or older	Younger than 18 years old
Cardiogenic shock refractory to conventional therapy, requiring VA-ECMO implantation	Written informed consent cannot be collected

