## Statistical analysis

The association of conventional measures of LV function, myocardial work and patient outcome will be assessed by logistic regression, and for certain objectives (ventilator free days, VA-ECMO free days) by linear regression. Despite the limited sample size, a large event rate can be expected in most of the outcome measures, potentially enabling multivariate logistic analyses. Collinearity of variables will be tested at each multivariable model by variance inflation factor (excessive if variance inflation factor >3). To examine the potential added prognostic value of myocardial work to other parameters, the constructed multivariable models will be compared based on Akaike Information Criterion (AIC). Receiver operating characteristic (ROC) curves will be calculated to assess the discriminatory power of the relevant parameters with regards to the study endpoints. Youden index will be used to quantify the optimal cutoff points of each parameter. These cutoff values will be used to dichotomize the study population. Outcomes of the dichotomized groups will be visualized using Kaplan-Meier curves and compared by the log-rank test. All statistical analyses will be performed using SPSS Statistics (IBM Software Group, Armonk NY, USA). A *P*-value of <0.05 will be considered statistically significant.

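### Kaplan-Meier and log-rank are planned for the marker groups' outcomes without restriction, although death competes with most of those outcomes, including the primary composite

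*Protocol article*

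**What the plan says.** The Statistical analysis section of the protocol article assigns logistic regression to the associations with outcome, and linear regression to two named objectives, ventilator-free and VA-ECMO-free days. ROC curves are then used "to assess the discriminatory power of the relevant parameters with regards to the study endpoints", and the Youden index gives a cutoff for each parameter. Two sentences follow: "These cutoff values will be used to dichotomize the study population" and "Outcomes of the dichotomized groups will be visualized using Kaplan-Meier curves and compared by the log-rank test". Neither names an endpoint, and nothing is said about how a death enters a curve for another event.

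The Study objectives section lists, among the secondary outcomes, "Successful weaning from mechanical ventilation at 30 days", "Discharge from intensive care unit (ICU) at 30 days" and "Discharge from hospital at 30 days", next to "All-cause mortality at 30 days". The primary outcome combines cardiovascular death, long-term mechanical circulatory support and heart transplantation at 30 days. Other deaths are not part of it.

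The section Sample size and patient population plans enrolment "with no loss to follow-up".

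**The concern.** A patient who dies on the ventilator can no longer be weaned from it or discharged. An ordinary Kaplan-Meier curve for such an event censors the patient at death. The estimate then treats that patient as if the event could still happen later, at the rate seen in those who remain. The same applies to a patient who dies of a non-cardiovascular cause in a curve for the primary composite.

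With no loss to follow-up, nearly all censoring before day 30 would be by death. The study's premise is that the markers predict outcome, so this censoring would probably differ between the groups being compared. The curves would not show the proportion of patients who had the event by day 30, and the gap between them would not be the gap in those proportions. A reader would see a picture of marker separation that could differ, in either direction, from what happened to the patients.

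**Working it through.** **Which outcomes are exposed.** All-cause mortality has no competing death, so Kaplan-Meier is suitable there. Ventilator weaning, ICU discharge and hospital discharge compete with death from any cause. The primary composite competes with non-cardiovascular death.

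**Inputs.** The article gives no death or recovery rates by marker group and no figure on this point to reproduce. All rates below are assumptions. D is the proportion dead by day 30 and R the proportion with the recovery event (for example hospital discharge) by day 30. Follow-up is complete.

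**Formula.** The true quantity is R. If the hazards of death and recovery stay in constant proportion, the total cumulative hazard is −ln(1 − D − R), and the share R/(D + R) belongs to recovery. With deaths censored at death, the expected curve at day 30 is

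1 − KM = 1 − exp[ ln(1 − D − R) × R/(D + R) ].

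**Example 1: the difference shrinks.**
- Group with more deaths, D = 50%, R = 20%: 1 − exp[ln(0.30) × 0.20/0.70] = 29.1%
- Other group, D = 15%, R = 50%: 1 − exp[ln(0.35) × 0.50/0.65] = 55.4%
- True difference 50 − 20 = 30 points; curves show 55.4 − 29.1 = 26.3 points.

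**Example 2: the difference widens.**
- D = 50%, R = 20%: 29.1%, as above
- D = 30%, R = 60%: 1 − exp[ln(0.10) × 0.60/0.90] = 78.5%
- True difference 60 − 20 = 40 points; curves show about 49 points.

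**Example 3: a difference appears where none exists.**
- D = 40%, R = 40%: 1 − exp[ln(0.20) × 0.40/0.80] = 55.3%
- D = 20%, R = 40%: 1 − exp[ln(0.40) × 0.40/0.60] = 45.7%
- True difference 0; curves show 55.3 − 45.7 = 9.6 points in favour of the group with more deaths.

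| Example | Overstatement, group with more deaths | Overstatement, other group | True difference | Difference on curves |
|---|---|---|---|---|
| 1 | 9.1 | 5.4 | 30 | 26 |
| 2 | 9.1 | 18.5 | 40 | 49 |
| 3 | 15.3 | 5.7 | 0 | 10 (reversed) |

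Recovery is overstated in both groups each time. Which group is inflated more changes with the rates.

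**Timing.** In Example 1, if every death preceded every discharge, the curves would show 0.20/0.50 = 40% and 0.50/0.85 = 59%, a gap of 19 points. If every discharge preceded every death, nobody would be censored before a discharge and the true 30 points would be shown.

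**Direction over a grid.** Rates of 10% to 70% in steps of 5 points were combined so that one group had higher death and lower recovery, which gave 4,164 combinations. The difference shrank in 57% and widened in the rest. With a mortality gap of at least 15 points, it shrank in 69%.

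**Check of the remedy.** If patients who die stay in the risk set, event-free, to day 30, no one is censored early. Then 1 − KM at day 30 equals R exactly, that is 20% and 50% in Example 1.

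**Primary composite.** The same formula applies, with D the proportion dying of non-cardiovascular causes. The article does not split deaths by cause, so no size is given. If such deaths are few, the distortion is small.

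**The case against.** The strongest reply is that the article does not say what the concern needs. The Kaplan-Meier sentence names no endpoint, and nothing states that deaths are censored. The secondary outcomes are defined as status at 30 days and are covered by logistic or linear regression, so the curves may be meant only for mortality and failure to wean. If deaths are coded as event-free to day 30, there is no bias at all. Which endpoints get a curve, and how deaths are coded in it, could be settled in an analysis plan that is not shown. Finally, a log-rank test with deaths censored is a legitimate comparison of event rates among patients still alive.

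Much of this stands. Use of the curves for discharge and weaning is inferred from an unrestricted sentence, and censoring at death from standard practice. Still, the same paragraph restricts linear regression to named objectives, while the curves follow directly on ROC cutoffs built for the study endpoints generally, so the broad reading is the natural one. The narrow reading does not remove the point either, because failure to wean has a competing death of its own. The log-rank defence covers the test as a comparison of rates among survivors, but not the curve read as a probability by day 30.

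A reader might infer that the curves will understate the separation between marker groups, because the group with more deaths is inflated most. The documents do not support this: they give no rates by group, and Examples 2 and 3 go other ways. A reader might also infer that the curves and the logistic models must contradict each other. That too depends on censoring at death, which the article does not state.

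**Conclusion.** The point holds as a mismatch between a stated, unrestricted method and a list of outcomes most of which have a competing death. If deaths are censored in the usual way, the event probability is overstated in both groups and the comparison is distorted in an unpredictable direction. In the assumed examples, 30 points becomes 26, 40 becomes 49 and 0 becomes 10. These figures rest on assumed rates, complete follow-up and hazards in constant proportion; other timings change them.

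The reach is limited. The logistic models, their AIC comparison and the ROC analyses do not depend on censoring and are unaffected, so a reader should not conclude that the main prognostic question is compromised. Because the direction is unknown in advance, the handling of death should be fixed before the data are seen. This is a cheap improvement.

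**What to change.** State in the Statistical analysis section, or in the analysis plan, which outcomes receive curves, and reserve standard Kaplan-Meier and log-rank for all-cause mortality at 30 days.

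For ventilator weaning, ICU discharge and hospital discharge, plot cumulative incidence with death as the competing event and compare groups by Gray's test. Do the same for the primary composite, with non-cardiovascular death as the competing event.

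Given complete follow-up, an equivalent route is to keep patients who have the competing death in the risk set, event-free, until day 30. The ordinary Kaplan-Meier and log-rank procedures in the planned software then give the cumulative incidence and the matching comparison.

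The cost is a few sentences of wording and a recoding of follow-up time at the competing death. The composite also needs cause of death, which its own definition already requires. No new data are needed. The downside is that the curves no longer describe the event rate among patients still alive. If that rate is of interest, it can be reported separately and labelled as such.

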### Study procedures

The most important collected clinical measures and examinations are summarized in Table 2. All the data will be recorded in a dedicated electronic case report form (eCRF), in line with General Data Protection Regulation (GDPR), in an anonymized manner. The detailed content of the eCRF is depicted in Supplementary Data S2.

**Table 2 T2:** Main collected clinical data.

Collected clinical data
Basic antropometric data
Medical history
Home medication
Indication of ECMO and details of clinical presentation
Parameters of ECMO support and venting
Medical therapy at TOE examination
Parameters of mechanical ventilation
Arterial blood gas data at the time of TOE
Hemodynamic data at the time of TOE
Right heart catheterization data at TOE (optional)
Laboratory data at the day of TOE

ECMO, extracorporeal membrane oxygenation; TOE, transoesophageal echocardiography.

Basic anthropometric data, relevant comorbidities and home medication will be recorded. Based on the given indication for MCS, the details of periprocedural clinical scenario will also be documented.

We will obtain relevant laboratory values at the day of the echocardiographic examination, and the current inotropic and vasopressor support, ventilator settings and most recent arterial blood gas data prior to the acquisition of the echocardiographic images. Right heart catheterization data will also be documented, if available.

### Echocardiographic examination

Echocardiographic acquisitions must be performed between 48 and 72 h following the initiation of MCS. Inotropic and vasopressor support at the time of the examination are based on the clinician's discretion. In order to ensure consistently high image quality, TOE is strongly recommended, however, in patients with good transthoracic echocardiographic window and with relevant concerns regarding TOE (e.g., awake and extubated, clinically relevant oropharyngeal bleeding), transthoracic approach is also acceptable. ECG-gated images and loops will be obtained and at least 3 cardiac cycles will be recorded. The detailed TOE acquisition protocol is depicted in Supplementary Data S1.

3D echocardiographic loops are not mandatory parts of the protocol, however, the acquisition of such datasets are strongly encouraged.

Two sets of acquisitions will be obtained: the first set will be performed with the current MCS minute volume. The second set will be recorded after setting a predefined minute support normalized to the body surface area of the patient (1.1 L/m^2^/min). After changing to the predefined MCS minute volume, only a short (1 min) waiting period is recommended, as the common clinical experience is that biventricular load rapidly changes along with the altered MCS settings.

In order to calculate non-invasive myocardial work indices, systolic and diastolic blood pressure will be recorded at the beginning of both acquisition sets. If the LV does not eject at the time of echocardiographic examination, mean arterial pressure will be used.

Echocardiographic measurements will be performed offline in an Echocardiography Core Laboratory (Semmelweis University, Heart and Vascular Center, Budapest, Hungary) by an experienced operator, blinded to the clinical data and outcome of the patients. All participating sonographers of the Centers will be certified by the Echocardiography Core Laboratory according to the international standards (22).

Cardiac chamber quantification will be based on the most recent guidelines. LV volumes and ejection fraction (EF) will be calculated using the biplane Simpson method. LV longitudinal strain will be measured using dedicated software (TomTec 2D AutoStrain, TomTec Imaging Systems, Unterschleissheim, Germany). LV non-invasive myocardial work indices will be calculated using the exported longitudinal strain data of TomTec and a custom-made software. The principles of myocardial work estimation will correspond with the calculation method of Russell et al. (23).

First, the opening and closure timepoints of the aortic and mitral valves are identified on the echocardiographic loops by visual assessment on a medoesophageal long-axis view. Next, using these temporal reference points, both curves are dissected into four sections (isovolumetric contraction, ejection, isovolumetric relaxation, and diastolic filling), with each section of the strain curve being matched with the corresponding section of the simulated pressure tracing. Due to the different temporal resolution of the datasets, the timestamps of the pressure and strain tracings are normalized in each section. The strain values are interpolated for the timestamps based on the LV pressure recording. The four sections of the recordings are subsequently concatenated, and pressure-strain loops are plotted. The instantaneous power is calculated by multiplying the strain rate (obtained by differentiating the strain curve) and the instantaneous LV pressure.

Global myocardial work index (GWI) is computed by integrating the power from mitral valve closure until mitral valve opening. Work performed during myocardial stretching means energy loss and was defined as negative work in contrast to positive work performed during myocardial shortening. Global constructive work index (GCW) is the sum of global positive work, while global wasted work (GWW) is the sum of negative global work. As a measure of global myocardial efficiency, global work efficiency (GWE) is also calculated as the ratio of the wasted work to the constructive work.

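### The protocol offers four overlapping myocardial work indices at two pump flows and does not say which index and flow set answer the main question, so both the P<0.05 test and the AIC comparison favour finding something by chance

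*Protocol article*

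**What the plan says.** The section on the echocardiographic examination defines the candidates:

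- **GWI:** "Global myocardial work index (GWI) is computed by integrating the power from mitral valve closure until mitral valve opening".
- **GCW and GWW:** "Global constructive work index (GCW) is the sum of global positive work, while global wasted work (GWW) is the sum of negative global work".
- **GWE:** "global work efficiency (GWE) is also calculated as the ratio of the wasted work to the constructive work".

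The same section plans acquisition at two pump flows: "Two sets of acquisitions will be obtained: the first set will be performed with the current MCS minute volume". The second follows a change to 1.1 L/m²/min after a recommended wait of one minute. Systolic and diastolic pressure are taken at the start of each set, expressly for the work calculation, so every index can be computed at both flows.

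The section on statistical analysis treats work as one undivided predictor: "The association of conventional measures of LV function, myocardial work and patient outcome will be assessed by logistic regression". A P value "of <0.05 will be considered statistically significant". Added value over other parameters is to be read from AIC comparisons of multivariable models. Each parameter gets its own Youden cutoff, followed by a log-rank test.

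The section on assessment of endpoints makes the main objective the superiority of work indices (plural) over conventional LV measures such as EF, GLS and outflow-tract VTI, with a further comparison against the SAVE score. Its two patient examples use GWI, but GWI is not named as primary, and neither is a flow set. No adjustment for multiplicity is mentioned.

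**The concern.** The protocol fixes one primary endpoint, failure to wean at 30 days, but leaves the predictor open. The predictor is half of the primary question in a prognostic study. With several versions available and none designated, the index and flow that look best can be chosen after the outcomes are known. A nominal 5% test then no longer carries a 5% error rate, and an AIC comparison made with the best of several candidates is optimistic. What is at stake is the study's central claim, that myocardial work adds prognostic information to the established measures.

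**Working it through.** **The plan's own figures.** The only error rate stated is P<0.05 per test; there is no family-wise figure to reproduce. The 92.2% power (100 patients, 30% failure, a 20% effect) cannot be reproduced with certainty because the scale of the effect is undefined. Risk-difference readings with 100 patients in total give about 45–81%; an AUC of 0.70 against 0.50 with 30 events and 70 non-events gives 91.4%. The present point does not depend on it.

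**Inputs from the protocol.** Four indices, two flow sets, 4 × 2 = 8 candidates; α = 0.05, sidedness not stated, two-sided assumed; n = 100 with 30% events, about 30 events.

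**Ceiling under independence.** 1 − 0.95^8 = 33.7% for eight tests; 1 − 0.95^4 = 18.5% for four.

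**Why that ceiling is not reached.** GCW and GWW are the positive and negative parts of the work. GWI is in essence GCW − GWW (assuming the same integration window) and GWE is GWW/GCW. That leaves about two free quantities per flow, both sets coming from the same patient a short time apart. As a rough guide, two effective tests give 1 − 0.95² = 9.8% and four give 18.5%. Because the derived indices are further looks at the same data, simulation is needed.

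**Simulation under the null.** GCW and GWW were generated at two flows, with GWI and GWE computed from them as above; n = 100, about 30% events. Two versions were run:

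| Chance of at least one P<0.05 | Univariable Wald test | Likelihood-ratio test, adjusted for a prognostic base marker |
|---|---|---|
| Eight (four indices, two flows) | 12–20% | 17–25% |
| Four indices, one flow | 9–11% | 13–16% |
| One designated index | 3–5% | 5–6% |

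The Wald results for eight cover between-flow correlations from 0.95 (12–14%) to 0.5 (17–20%). The Wald test is somewhat conservative here, which is why its column is lower. Taking both together: about 12–25% for eight and 9–16% for four.

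**AIC.** AIC = 2k − 2 log L. Adding one parameter lowers AIC when the likelihood-ratio statistic exceeds 2. For a null predictor that has probability P(χ²₁ > 2) = 15.7% in large samples, and 17–18% in the adjusted simulation. With eight candidates, at least one lowered AIC in 44–58% of null studies.

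**Price of adjusting instead of designating.** Bonferroni over eight uses 0.05/8 = 0.00625. Power of 92.2% at two-sided 0.05 corresponds to a shift of 1.960 + 1.419 = 3.379. The new critical value is 2.734, so power becomes Φ(3.379 − 2.734) = Φ(0.645), about 74%.

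**The case against.** The strongest reply is that this is a condensed article on an observational study, and that the choice of predictor and the handling of multiplicity may sit in an analysis plan that is not shown. That limits how firmly the point can be put. It does not remove it: the protocol states its main objective, its threshold and its model comparison, and on those terms more than one predictor can answer the question.

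Four stronger readings are tempting, and the document does not support them:

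- *That all eight values will be tested.* The text describes acquisition at two flows and analysis of myocardial work. It does not say which set enters the prognostic models. All eight are available and none is excluded; that is as far as it goes.
- *That the false-positive chance reaches 34%.* This needs eight independent tests, which the definitions of the indices rule out.
- *That work has far more chances than each conventional measure.* Both sets are image acquisitions, so EF, GLS and VTI can also be taken at both flows, and the list of conventional measures is open-ended. Only SAVE clearly has a single value.
- *That the second set was normalised so that patients can be compared.* The protocol gives no such reason. Preferring that set is a reviewer's suggestion.

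It is also fair to object that a P value does not by itself decide the superiority question, since added value is judged by AIC. That is correct, but AIC is the more permissive criterion here, as the figures show.

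**Conclusion.** The point holds in this form: the protocol leaves open which myocardial work index, at which pump flow, answers its main question, while applying an unadjusted P<0.05 and an AIC comparison. If all eight values are used, the chance of at least one false association on the primary endpoint is about 12–25%, roughly two to five times nominal. With four indices at one flow it is about 9–16%, roughly two to three times. Under AIC, at least one null index appears to improve the model in about 44–58% of studies, against about 17% for one index.

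The direction is secure; the sizes are not exact. The document gives no distributions or correlations for the indices, so log-normal work components and between-flow correlations of mainly 0.5 to 0.95 were assumed. Log-rank tests at Youden cutoffs derived from the same patients, and the seven secondary outcomes, would add to the error and are not counted.

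**What to change.** Before core-laboratory values are linked to outcomes, state in the analysis section:

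1. One index at one flow set is the primary predictor. GWI at the predefined body-surface-normalised flow is one reasonable choice, since the protocol's own examples use GWI and that set is taken at a common normalised flow. This selects an analysis variable only and changes nothing in how pump flow is managed.
2. That predictor alone is used for the primary two-sided 5% test on failure to wean and for the primary AIC comparison with EF, GLS, VTI and SAVE. The conventional echocardiographic measures come from the same flow set.
3. The same index at the other flow is a named sensitivity analysis. The remaining indices and the secondary outcomes are exploratory, reported with intervals, or Holm-adjusted.

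The cost is a few sentences and no patients. Designation returns the primary test to about 5% without the power loss of a Bonferroni correction over eight. The downside is that an index or flow that performs better than the designated one can only be hypothesis-generating.

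### Blood pressure for the work indices is read at the start of each acquisition set, with no stated reading at the strain loops and no check that pressure has held

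*Protocol article*

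**What the plan says.** All of this is in the protocol article.

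- **Two sets (Echocardiographic examination).** For the first, "the first set will be performed with the current MCS minute volume". For the second, "The second set will be recorded after setting a predefined minute support normalized to the body surface area of the patient", the target being 1.1 L/m²/min.
- **Wait before set 2 (same section).** After the change, "only a short (1 min) waiting period is recommended". The reason given is that "the common clinical experience is that biventricular load rapidly changes along with the altered MCS settings".
- **Pressure (same section).** For the work calculation, "systolic and diastolic blood pressure will be recorded at the beginning of both acquisition sets". Mean arterial pressure is substituted if the ventricle does not eject.
- **Calculation (same section).** The pressure curve is simulated and aligned by valve events, "with each section of the strain curve being matched with the corresponding section of the simulated pressure tracing". Then: "The instantaneous power is calculated by multiplying the strain rate (obtained by differentiating the strain curve) and the instantaneous LV pressure".
- **Vasoactive support.** The same section leaves it to the clinician's discretion at the time of the examination. Study procedures says that the team will obtain the "current inotropic and vasopressor support, ventilator settings and most recent arterial blood gas data prior to the acquisition" of the images.
- **Main objective (Assessment of endpoints).** The question is whether the work indices are better prognostic markers than conventional measures such as EF, GLS and outflow-tract VTI.

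**The concern.** Work is a product of pressure and strain rate, so the pressure should describe the beats from which the strain is taken. The stated rule ties it to the start of the set instead. A set takes time: it has to supply views for biplane volumes, strain, valve timing and outflow-tract VTI, and 3D loops are encouraged. In set 2 the reading also follows a deliberate change in support. The reason given for the short wait is that load moves quickly. It does not say that arterial pressure has stabilised or will stay constant during the set.

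If pressure moves between the reading and the strain loop, the error enters the work indices only. GLS, EF and VTI use no pressure. The study's main comparison would then set a marker carrying extra measurement error against comparators that do not carry it. A change in vasoactive support during set 2 could cause such a movement, and the article describes only support before imaging.

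**Working it through.** The plan states no figure on this point, so there is nothing to reproduce. The check has three steps.

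**1. How a pressure error enters each index.** Power is pressure × strain rate, and GWI is its integral from mitral valve closure to mitral valve opening. If the recorded pressure is *k* times the pressure at the loop throughout the cycle, then

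∫ *k*·P·(strain rate) dt = *k* · ∫ P·(strain rate) dt.

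Numerical integration with *k* = 0.95, 0.90, 0.85 and 0.80 returned 0.95, 0.90, 0.85 and 0.80 of the reference work. A 15% discrepancy in pressure is thus a 15% error in GWI, and likewise in GCW and GWW. GWE is defined as a ratio of wasted to constructive work, so *k* cancels as far as the error is proportional. GLS, EF and VTI do not contain *k*.

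**2. Random drift.** Let the recorded work be the true work × (1 + e), where e has mean zero and SD *c*, independent of everything else. With between-patient coefficient of variation CV,

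reliability = CV² / [CV² + c²(1 + CV²)].

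The documents give neither CV nor *c*, so both are assumed:

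| Assumed CV of GWI | c = 5% | c = 10% | c = 20% |
|---|---|---|---|
| 0.4 | 0.16/0.1629 = 0.98 | 0.16/0.1716 = 0.93 | 0.16/0.2064 = 0.78 |
| 0.6 | 0.36/0.3634 = 0.99 | 0.36/0.3736 = 0.96 | 0.36/0.4144 = 0.87 |

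**3. Effect on discrimination.** This was simulated with GWI taken as GLS × pressure. Assumptions are 30% failures (the rate in the sample size section), pressure CV 20% and random drift SD 10%.

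- *Same 15% fall in every patient* (GLS CV 30–40%, GLS difference 0.3–0.4 SD): AUC 0.595 with the start-of-set pressure and 0.591 with the pressure at the loop. With the smaller GLS difference it is 0.571 and 0.567. Every work value is 15% wrong, yet discrimination is not lost.
- *Purely random drift:* AUC changes by about 0.01 or less.
- *Fall of 10–20% in failing patients only* (modest GLS difference): AUC 0.65–0.71 with pressure at the loop, 0.59 with the start-of-set pressure. Other assumed GLS settings gave 0.64–0.74 against 0.58–0.60.
- *Fall of 20% in failing patients and 5% in the others:* 0.68 against 0.59.

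In the last two cases the gap arises because the assumed fall itself carries information on outcome. These figures show what would be needed for a material effect; they do not estimate one.

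**The case against.** A reader might infer that work at the fixed flow combines pressure and strain from two different haemodynamic states. The text does not support that. Set 2 is recorded after the flow has been set, and its pressure is taken at the beginning of that same set, so both belong to one flow setting. A mismatch would need drift that continues after the wait, and the article neither shows nor concedes any. Nor does it give the patient's prior flow, so the size and direction of the change are unknown. An argument that failing ventricles let pressure fall presumes a reduction in support and outcome-dependent drift.

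Further points on that side also stand. The order and duration of the loops are referred to Supplementary Data S1 and the eCRF content to S2, and neither is shown. The strain views may already come first, and therapy and pump settings may already be captured per set. Further pressure readings are not ruled out. Set 1 has no flow change before it. The method is built on a simple cuff-type input to a simulated curve and does not claim a simultaneous tracing.

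What does not fall away is the timing rule. The article itself ties the pressure used for work to the start of the set, and a favourable view order in S1 would shorten the interval without changing that rule. A pressure not captured at the loop may not be recoverable later at the core laboratory.

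**Conclusion.** The point holds as a measurement risk that is cheap to remove. It is not a contradiction or a demonstrated error. Pressure and strain may come from different moments, mainly in set 2, and any proportional difference passes in full into GWI, GCW and GWW but not into the measures with which they are to be compared.

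The size cannot be derived from the documents and may be negligible. Random drift of 5–10% would cost little (reliability about 0.93–0.99), and 20% would cost more (about 0.78–0.87), both under the assumed CVs of 0.4 and 0.6. A uniform shift would leave discrimination essentially intact, although it would move the GWI values from which the planned Youden cut-offs are derived. A material loss of AUC requires drift that differs between patients who fail and those who do not. That is plausible but assumed, and the AUC gaps above should not be read as an expected bias.

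**What to change.** In Echocardiographic examination, amend the pressure rule as follows:

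- Record systolic, diastolic and mean arterial pressure when the views used for strain are acquired, in each set, and calculate the work indices from those values.
- Keep the start-of-set reading, so that the change between the two readings can be reported by set and by outcome. If drift proves negligible, the data will show it.
- In Study procedures, record the vasoactive support in force at each set, in addition to that before imaging.

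If S1 or S2 already provides for any of this, the article's wording should be aligned with it. The cost is a few more eCRF entries per examination. No procedure, staff, patients or change in treatment is added.
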